### Primary and secondary endpoints/outcome measures

*The primary objective of this study will be:***immunological efficacy**, assessed by quantification of circulating immune effectors specific for a selected panel of tumor antigens. In particular, this panel will include tumor antigens known to be highly expressed in over 80% of patients with melanoma or RCC in and whose expression must be confirmed in tumor biopsies taken before and after at least 2 cycles.

*The secondary objectives will be***assessment of the predictive value of pretreatment serum biomarkers** in identifying patients who will probably benefit from high-dose IL-2 based therapy. In particular, pretreatment concentrations of VEGF, fibronectin and proinflammatory cytokines (IL-1beta, IL-6, IL-8, IL-10, IL-12, alphaTNF) will be evaluated by SearchLight multiplex array analysis. Expression of CAIX in pretreatment biopsies from RCC patients will be evaluated by immunohistochemistry. In melanoma patients, tumor tissue biopsied before the start of treatment will be evaluated for the presence of N-Ras mutations.**toxicity, response rate and overall survival.**

Patients will be evaluated every 8 weeks by computed tomography imaging to determine the clinical response, and every 3 months after completion of treatment until death. The time of disease progression and the initiation of alternative therapies will also be recorded.

### Study population

Patients with metastatic melanoma or renal cell carcinoma with measurable disease, life expectancy of at least 3 months and with tissue sample availability.

### Inclusion criteria

 Patients must have histologically or cytologically confirmed non resectable stage III or IV advanced melanoma or renal cell carcinoma (RCC). Patients must have a minimum of two lesions, one of which must be measurable (*i.e.* a lesion that can be accurately measured in at least one dimension with longest diameter >20 mm using conventional techniques or >10 mm using spiral CT scan). At least one tumor lesion accessible for bioptic sampling. Prior lines (maximum 4) of chemotherapy, immunotherapy or biological therapy (*e.g.* inhibitors of B-Raf or c-Kit, ipilimumab, etc.) for advanced disease are allowed (patients must have finished prior treatments at least 4 weeks before the first IL-2 dose). Male or female, aged >18 years. Life expectancy > 3 months. ECOG performance status <1. Patients must have normal organ and marrow function:ECG and echocardiogram within normal institutional limits.Pulmonary function tests within normal institutional limits (only to be performed in patients with lung metastases or history of impaired lung function). No contraindication for the use of vasopressor agents. Female participants of child bearing potential and male participants whose partner is of child bearing potential must be willing to ensure that they or their partner use effective contraception during the study and for 3 months thereafter. Participant is willing and able to give informed consent for participation in the study.

### Exclusion criteria

The participant may not enter the study if ANY of the following apply: Patient with stage I or II melanoma or RCC. Patients who have had chemotherapy or radiotherapy or immunotherapy within 4 weeks (6 weeks for nitrosoureas or mitomycin C) prior to entering the study or those who have not recovered from adverse events due to agents administered more than 4 weeks earlier. Participation in another clinical trial with any investigational agents within 30 days prior to study screening. Patients with known brain metastases should be excluded from this clinical trial because of their poor prognosis and because they often develop progressive neurologic dysfunction that would confound the evaluation of neurologic and other adverse events. History of allergic reactions attributed to compounds of similar chemical or biologic composition to IL-2 or other agents used in the study. Any autoimmune disease which could be exacerbated by IL-2. A medical illness requiring chronic treatments with corticosteroids or other immunosuppressive agents. A history of significant cardiovascular disease, including myocardial infarction, congestive heart failure, primary cardiac arrhythmias, angina pectoris or cerebrovascular accident. Uncontrolled intercurrent illness including, but not limited to, ongoing or active infection, symptomatic congestive heart failure, unstable angina pectoris, cardiac arrhythmia, or psychiatric illness/social situations that would limit compliance with study requirements. Other known malignant neoplastic diseases in the patient’s medical history with a disease-free interval of less than 5 years (except for previously treated basal cell carcinoma and *in situ* carcinoma of the uterine cervix). HIV-positivity, whether or not symptomatic.

### Study treatment

#### Radiotherapy

Radiotherapy will be administered in three daily doses of 6–12 Gy (depending on the volume and anatomic location of irradiated lesion) to 1–5 non-index metastatic fields. The reference isodose will be 60-70%/isodose, with an increased dose distribution inside the tumor. Radiotherapy techniques permitting a rapid decrease of the dose distribution outside the target (IMRT-IMAT) will be used. Pre-treatment XRT will be scheduled to finish on day −2 or −1. Radiotherapy will be performed twice, before the first and third IL-2 cycles.

#### High-dose IL-2

The treatment is based on high-dose IL-2: 18 MIU/m2/day in 500 cc administered by continuous IV infusion over 72 hours. The administration of IL-2 will take place on an inpatient basis. The first day of IL-2 therapy is considered as Day +1. Treatment with IL-2 will be administered every 3 weeks for up to 4 cycles, then every 4 weeks for a further 2 cycles.

#### Concomitant medications

During the 3rd day of IL-2 infusion, the following will be administered:3 bolus/day of desametazone 4 mg;Ondansetron 8 mg ×2/day;Paracetamol 500 mg ×3/day;Adequate i.v. hydration.

### Dose delays/modifications

NCI Common Toxicity Criteria version 4.0 (available at: http://www.eortc.be/services/doc/ctc/CTCAE_4.03_2010-06-14_QuickReference_5x7.pdf) will be used. No dose reductions of IL-2 are allowed. Dose delays within the same cycle: IL-2 doses will be delayed on the basis of the symptomatic recovery from the previous dose. A delay longer than 24 hours will result in discontinuation of that cycle of IL-2.

### Study treatment modifications

Guidelines for delay or discontinuation of IL-2 are given in Tables 1 and Table 2. The presence of relative criteria implies that a patient is nearing the completion of a cycle of therapy and that with appropriate corrective measures or with a time delay to allow for recovery, it may be safe to administer another IL-2 dose. Several relative criteria that are not easily reversible or correctable are usually an indication that treatment should be discontinued. The presence of an absolute criterion that is not easily reversible is also generally considered an indication to interrupt IL-2.

**Table 1 Tab1:** **Guidelines for delay or discontinuation of IL-2: relative and absolute criteria**

**System**	**Relative criteria**	**Absolute criteria**
***Cardiac***	- Sinus tachycardia (120–130 beats per minutes);	- Sinus tachycardia (>130 beats per minutes persists after correcting hypotension, fever and stopping dopamine);
		- Atrial fibrillation;
		- Supraventricular tachycardia;
		- Ventricular arrhythmia;
		- Elevated creatine kinase isoenzymes or troponin;
		- Electrocardiogram changes of ischemia;
***Dermatologic***	---	- Moist desquamation;
***Gastrointestinal***	- Diarrhea, up to 6 episodes/day	- Diarrhea, > 6 episodes/day
	- Ileus/abdominal distension;	- Severe abdominal distention affecting breathing;
	- Bilirubin >7 mg/dl;	- Severe abdominal pain, unrelenting;
***Hemodynamic***	- Maximum neosynephrine 1–1.5 mcg/kg/min;	- Maximum neosynephrine 1.5-2 mcg/kg/min;
	- Maximum neosynephrine >0.5 mcg/kg/min;	- Maximum neosynephrine >0.8 mcg/kg/min;
***Hemorrhagic***	- Guiac + sputum, emesis, stool;	- Frank blood sputum, emesis, stool;
	- Platelets 30,000-50,000/mm^3^;	- Platelets <30,000/mm^3^;
***Infections***	---	- Strong clinical suspicion or documented;
***Muscoloskeletal***	- Weight gain >15%;	
	- Extremity tightness;	- Extremity paresthesias;
***Neurologic***	- Vivid dreams;	- Hallucination;
	- Emotional lability;	- Persistent crying;
		- Mental status changes not reversible in 2 hours;
		- Inability to subtract 7 s or spell “world” backwards
		disorientation;
***Pulmonary***	- Resting shortness of breath;	- >4 L O2 nasal cannula for saturation >95% or 40% O2 mask for saturation >95%;
	- 3-4 L O2 nasal cannula for saturation >95%;	- Moist rates involving more than half of both lung fields;
	- Moist rates involving more than half of both lung fields;	- Endotracheal intubation;
		- Pleural effusion requiring tap or chest tube;
***Renal***	- Urine 80–160 ml/shift;	- Urine <80 ml/shift;
	- Urine 10–20 ml/h;	- Urine <10 ml/h;
	- Creatinine 2.5-2.9 mg/dl.	- Creatinine >3 mg/dl.

**Table 2 Tab2:** **Guidelines for delay or discontinuation of IL-2 based on the number of assessed relative or absolute criteria**

**Observation category**	**Action**
***Any relative criteria***	- Initiate corrective measure +/− delayed IL-2;
***Three criteria***	- Initiate corrective measure +/− delayed IL-2, stop IL-2 if not easily reversible;
***Any absolute criteria***	- Initiate corrective measure +/− delayed IL-2, stop IL-2 if not easily reversible.

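### Table 1 gives two incompatible neosynephrine limits for stopping IL-2 and lists one lung sign as both a relative and an absolute criterion

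*Protocol article*

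**What the plan says.** The section Study treatment modifications says "Guidelines for delay or discontinuation of IL-2 are given in Tables 1 and Table 2". In the Hemodynamic part of Table 1 there are two rows:

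- Row 1: relative "Maximum neosynephrine 1–1.5 mcg/kg/min"; absolute "Maximum neosynephrine 1.5-2 mcg/kg/min".
- Row 2: relative "Maximum neosynephrine >0.5 mcg/kg/min"; absolute "Maximum neosynephrine >0.8 mcg/kg/min".

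In the Pulmonary part, the entry "Moist rates involving more than half of both lung fields" stands in the relative column and, word for word, in the absolute column.

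Table 2 turns these classes into actions. One relative criterion calls for correction, with an optional delay. Three criteria, or "Any absolute criteria", add the instruction "stop IL-2 if not easily reversible". The section Dose delays/modifications rules out reducing the IL-2 dose and ends a cycle once a delay passes 24 hours.

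**The concern.** The two hemodynamic rows share drug, label and unit, and nothing in the article says how they differ or which one governs. A patient on 1.2 mcg/kg/min meets only a relative criterion by row 1 and an absolute one by row 2. The lung sign has the same problem without any number: one finding belongs to both classes.

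Because the IL-2 dose may not be reduced, holding or stopping the infusion is what staff can do about dosing, and the class of the criterion decides whether stopping is called for. The entries concern vasopressor need and lung findings during an infusion whose daily dose, given over 5 days, had capillary leak as its limiting toxicity according to the Background. Two clinicians could treat the same patient differently, each following a printed limit.

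**Working it through.** **Inputs.** The four neosynephrine entries and the two lung entries of Table 1; the actions in Table 2; the 24-hour rule in Dose delays/modifications; 18 MIU/m2/day for 72 hours from High-dose IL-2. The plan gives no figure of its own to reproduce here.

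**Step 1: classify each dose by each row as printed.**

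| Neosynephrine, mcg/kg/min | Row 1 | Row 2 |
|---|---|---|
| up to 0.5 | none | none |
| >0.5 to 0.8 | none | relative |
| >0.8 to <1.0 | none | absolute |
| 1.0 to <1.5 | relative | absolute |
| 1.5 | relative and absolute | absolute |
| >1.5 to 2 | absolute | absolute |
| >2 | none, read literally | absolute |

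Where row 2 meets both its limits, the table shows the higher class. The conflict that matters runs from above 0.8 to below 1.5. Row 1's relative band lies wholly inside row 2's absolute range. Two other bands also differ on paper but are not counted: between 0.5 and 0.8 neither row is absolute, and above 2 nobody would sensibly take row 1 to mean that no criterion is met. Row 1's own ranges share the endpoint 1.5, which is untidy but changes no action, since both rows are absolute there.

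**Step 2: is overlap normal in this table?** Relative against absolute for the other graded pairs: heart rate 120–130 vs >130; diarrhea up to 6 vs >6 episodes; platelets 30,000–50,000 vs <30,000; nasal oxygen 3–4 vs >4 L; urine per shift 80–160 vs <80 ml; urine per hour 10–20 vs <10 ml; creatinine 2.5–2.9 vs >3 mg/dl. Overlaps: 0 of 7. The overlap is therefore not a convention of the table.

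**Step 3: when does the instruction differ?** Take a finding that is not easily reversible, with no other absolute criterion and k other relative criteria. Read Table 2's three criteria as three or more (an assumption).

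- Absolute reading: stop for every k ≥ 0.
- Row 1 alone, 1.0 to <1.5: count is k + 1, so stop needs k + 1 ≥ 3, i.e. k ≥ 2. Instructions differ for k = 0 or 1.
- Row 1 alone, >0.8 to <1.0: count is k, so stop needs k ≥ 3. Instructions differ for k = 0, 1 or 2, and at k = 0 no action is triggered.
- Lung sign read as relative: count is k + 1, so stop needs k ≥ 2. Instructions differ for k = 0 or 1.

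**Step 4: what the 24-hour rule removes.** A hold of more than 24 hours ends the cycle under every reading. The difference survives only if IL-2 continues without a hold (Table 2 makes the delay optional), resumes within 24 hours, or no criterion is registered.

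**Step 5: drug still to be given.** One cycle is 18 × 3 = 54 MIU/m2. If the finding appears at 24 hours, 54 − 18 = 36 MIU/m2 remains; at 48 hours, 54 − 36 = 18 MIU/m2. Both onset times are assumptions. These figures show how much drug the decision concerns; they do not measure harm.

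**The case against.** The best answer is that Table 2 already settles the action. It attaches the stop instruction to any absolute criterion, so a dose above 0.8 mcg/kg/min qualifies whatever the line above says, and so does the lung sign. The laxer outcome requires staff to apply one line and overlook its neighbour. Both classes begin with the same corrective step, a relative criterion allows further IL-2 only after correction or recovery, and the 24-hour rule caps the delay. The tables are guidelines and reversibility is a bedside judgment, so the counts in Step 3 are more exact than the text they formalise. The Background also reports that the 72-hour schedule was well tolerated, and dexamethasone is added to lower the risk of capillary leak. The slip may exist only in the article.

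Most of this stands, and it limits the consequence. It does not remove the contradiction. If the stricter entry always wins, row 1's relative band and the lung sign's relative listing can never decide anything, so the table still contains wrong entries. If row 2 was meant for a different quantity, its label is wrong. A broken table in the PDF reading is an unlikely explanation: each hemodynamic row has one entry in each column, and the lung entry is complete in both.

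**Conclusion.** The concern holds. Table 1 contradicts itself for neosynephrine doses above 0.8 and below 1.5 mcg/kg/min (none against absolute below 1.0, relative against absolute from 1.0) and for one lung sign. The instruction to stop can differ when few other relative criteria are present: up to one, or up to two in the lower dose band. That count assumes that three criteria means three or more, that the finding is not easily reversible, and that staff apply the laxer entry alone. The document gives no frequency for these events, so the number of patients affected cannot be estimated. Sample size, decision rule and primary analysis are untouched. This should be fixed because it is a stopping threshold for a toxic inpatient treatment, but the expected consequence is small.

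**What to change.** Check the two hemodynamic rows and the lung sign against the source criteria and the full protocol. Then give each measure one relative and one absolute range that neither overlap nor share an endpoint. If the rows concern different quantities, label them so. List the lung sign, at a given extent, in one column only. Until that is done, add one sentence saying that the stricter (absolute) entry governs. The article does not show which values are correct, and none is proposed here.

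The cost is two table rows, one lung entry and one interim sentence. If only the article is wrong, an erratum is enough; if the full protocol carries the same entries, correct it by amendment or a letter to investigators. There is no statistical cost.

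### Table 1 (Renal) leaves a creatinine of 3.0 mg/dl in neither the relative nor the absolute column, so it counts for less in Table 2 than 2.9 does

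*Protocol article*

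**What the plan says.** Table 1 of the protocol article sorts toxicities into relative and absolute criteria for delaying or discontinuing IL-2. In the Renal row the relative creatinine criterion is "Creatinine 2.5-2.9 mg/dl" and the absolute one is "Creatinine >3 mg/dl".

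Table 2, titled "Guidelines for delay or discontinuation of IL-2 based on the number of assessed relative or absolute criteria", turns these into actions:
- Any relative criterion: corrective measures, with or without a delay of IL-2.
- Three criteria: the same, plus "stop IL-2 if not easily reversible".
- Any absolute criterion: "Initiate corrective measure +/− delayed IL-2, stop IL-2 if not easily reversible".

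The section Study treatment modifications introduces both tables as guidelines and adds: "Several relative criteria that are not easily reversible or correctable are usually an indication that treatment should be discontinued". The section Dose delays/modifications rules out dose reductions of IL-2 and ends a cycle once a delay exceeds 24 hours. No other section gives a creatinine threshold that would place 3.0 mg/dl.

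**The concern.** The two creatinine criteria do not meet. The relative band stops at 2.9 and the absolute criterion starts strictly above 3, so 3.0 belongs to neither. Because Table 2 works on which criteria are met and how many, a value that belongs to neither column adds nothing.

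A rule for withholding a toxic drug should never respond less as the laboratory value worsens. Here, read literally, it does. Since the IL-2 dose may not be reduced, delay and discontinuation are the dose controls that remain, and their thresholds should be unambiguous. A reader who notices the gap must also guess the column, and the choice matters: the relative row asks for corrective measures with optional delay, while the absolute row adds the stop clause.

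**Working it through.** **Inputs** (Table 1, Renal): relative set 2.5 ≤ c ≤ 2.9; absolute set c > 3, with c the creatinine in mg/dl.

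**Step 1: which column applies.**
- c = 2.9: 2.5 ≤ 2.9 ≤ 2.9, so relative.
- c = 3.0: 3.0 > 2.9, so not relative; 3.0 is not greater than 3, so not absolute. Neither column.
- c = 3.1: 3.1 > 3, so absolute.

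The uncovered interval is 2.9 < c ≤ 3.0. At one decimal, the precision printed in the table, it holds one value, 3.0. At two decimals it holds ten values, 2.91 to 3.00. The article states no reporting precision, so the two-decimal count is conditional on that assumption.

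**Step 2: what Table 2 then does.** The three-criteria row is read here as three relative criteria, since any absolute criterion has its own row. No absolute criterion from another organ system is assumed.

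| Other relative criteria | Creatinine | Column | Relative count | Table 2 outcome |
|---|---|---|---|---|
| 0 | 2.9 | relative | 0 + 1 = 1 | corrective measures, optional delay |
| 0 | 3.0 | none | 0 + 0 = 0 | no row applies |
| 0 | 3.1 | absolute | 0 | stop clause, through the absolute row |
| 2 | 2.9 | relative | 2 + 1 = 3 | stop clause, through the three-criteria row |
| 2 | 3.0 | none | 2 + 0 = 2 | corrective measures, optional delay |
| 2 | 3.1 | absolute | 2 | stop clause, through the absolute row |

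In both blocks the response at 3.0 is weaker than at 2.9 and at 3.1, so the printed rule is not monotone.

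**Step 3: is this how the table is built elsewhere?** In several other graded rows the columns meet. Platelets are "Platelets 30,000-50,000/mm^3" against "Platelets <30,000/mm^3". Urine is 80–160 against <80 ml/shift and 10–20 against <10 ml/h. Sinus tachycardia is 120–130 against >130, diarrhea is up to 6 against >6 episodes per day, and nasal oxygen is 3–4 L against >4 L. In each, the relative band includes the boundary and the absolute criterion starts just beyond it. These rows serve only as a comparison, and nothing is claimed about the rest of Table 1.

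**Step 4: could it be a lost symbol?** Unlikely. The ≥ sign is preserved in Table 3 of the same article.

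**The case against.** The gap itself is not in dispute; its importance is.

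- **The tables are guidelines.** The surrounding text leaves room for judgement, and a clinician who sees 2.9 flagged as relative and values above 3 as absolute would hardly treat 3.0 as normal. This is probably right and lowers the practical weight. It does not tell the clinician which column applies.
- **The narrative text may catch the two-plus-creatinine case.** It refers to several persistent relative criteria without fixing the number at three, so two could prompt discontinuation even when creatinine is not counted. This stands as mitigation. The loss of the stop clause shown above is therefore a reading of Table 2 alone.
- **The 24-hour limit is a backstop.** A delay beyond 24 hours ends the cycle anyway. That helps only once IL-2 has been delayed, and Table 2 makes delay optional.
- **The two-decimal count is an assumption, and rounding might shrink it.** It is an assumption. Rounding to one decimal, however, moves the gap rather than shrinking it: 2.91 to 2.94 become 2.9 and are covered, but 3.01 to 3.04 become 3.0 and drop out. The unassigned values are then 2.95 to 3.04, again ten.
- **The situation is rare and the intended column is unknown.** The document gives no basis for a frequency, and none is claimed. Placing 3.0 in the relative band would also close the gap.

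**Conclusion.** The concern holds as a literal error in a stated treatment-stopping threshold. A creatinine of 3.0 mg/dl is unassigned, and a worse value counts for less than a better one.

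The size is minor. One reportable value at one decimal is affected, and the difference is confined to whether creatinine counts at all and whether the stop clause applies. The relative and absolute rows of Table 2 begin with the same action, and another criterion such as urine output, or clinical judgement, may still prompt a response. The primary endpoint, the two-stage decision rule and the analysis population are untouched.

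The conclusion rests on reading both limits as printed. The two-criteria example rests further on reading the three-criteria row as three relative criteria, with no absolute criterion in any other system. This is worth correcting but is not an obstacle to the trial.

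**What to change.** In Table 1, Renal, write the relative criterion as creatinine 2.5 to <3.0 mg/dl and the absolute criterion as creatinine ≥3.0 mg/dl. Every value from 2.5 upward then falls in exactly one column at any reporting precision, and the rule becomes monotone in creatinine. A value of 3.0 counts as one absolute criterion, which is the cautious choice and agrees with the printed upper limit of 2.9.

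The article does not settle which column was intended for 3.0, so the sponsor's clinicians should confirm. If they prefer to treat 3.0 as relative, a band of 2.5 to 3.0 with the absolute criterion left at >3 also closes the gap.

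The cost is an edit to one table row, with no change to design, sample size or data collection.
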